## 1 Introduction

According to the latest global cancer statistics from 2018, lung cancer ranks first among all malignancies in both incidence and mortality. Lung cancer is also the leading cancer type in China. Histologically, lung cancer is primarily classified into two major subtypes: non-small cell lung cancer (NSCLC) and small cell lung cancer (SCLC). NSCLC represents the most common form, constituting approximately 80%–85% of all lung cancer cases.

Advances in lung cancer screening among high-risk populations have led to a steady increase in the detection of early-stage disease. For patients with stage I–IIIa NSCLC, surgical resection remains the cornerstone of treatment and the primary therapeutic strategy. Moreover, the role of adjuvant chemotherapy has been firmly established; platinum-based regimens are now considered standard adjuvant therapy for patients with completely resected stage II–IIIa NSCLC. Despite significant improvements in survival outcomes conferred by surgery and adjuvant chemotherapy, the 5-year overall survival rate remains suboptimal at approximately 40%.

Consequently, considerable clinical research efforts are currently focused on identifying additional therapeutic approaches to reduce recurrence risk and further improve long-term survival. In patients harboring activating epidermal growth factor receptor (EGFR) mutations, postoperative adjuvant therapy with EGFR tyrosine kinase inhibitors (TKIs) has been actively investigated. The BR.19 and RADIANT trials evaluated adjuvant TKI therapy in unselected populations with stage Ib–IIIa NSCLC but failed to demonstrate a significant improvement in disease-free survival (DFS) compared with placebo. However, results from the CTONG1104 trial (published in 2018) and the EVAN study (reported at the 2017 World Conference on Lung Cancer) demonstrated that, in patients

with completely resected EGFR-mutant NSCLC, adjuvant EGFR-TKI therapy conferred a statistically significant DFS benefit over conventional chemotherapy.

For patients with stage IIIa NSCLC, definitive concurrent chemoradiotherapy remains the standard of care for those deemed unresectable. In potentially resectable cases, neoadjuvant therapy followed by surgery is an accepted alternative; however, the optimal neoadjuvant regimen, whether chemotherapy alone, sequential chemoradiotherapy, concurrent chemoradiotherapy, or chemotherapy followed by concurrent chemoradiotherapy, remains to be definitively established. The advent of targeted therapies and immune checkpoint inhibitors has further expanded the landscape of neoadjuvant strategies. In 2018, the European Society for Medical Oncology (ESMO) reported findings from CTONG1103, the first global trial of neoadjuvant targeted therapy, which showed superior efficacy of neoadjuvant EGFR-TKIs over neoadjuvant chemotherapy in patients with resectable EGFR-mutant stage IIIA-N2 NSCLC. Meanwhile, trials such as NEOSTAR, NADIM, and LCMC3 have explored the use of programmed death-1 (PD-1) inhibitors in the neoadjuvant setting for resectable NSCLC, offering promising preliminary evidence for the potential of neoadjuvant immunotherapy.

NSCLC remains one of the most intensively researched areas in oncology, yet numerous critical questions persist. Surgical approaches for lung cancer are diverse and continually evolving, raising important questions regarding optimal technique selection and the extent of lymph node dissection, particularly in early-stage disease. Retrospective data suggest that, for clinical stage I NSCLC, thoracoscopic and robot-assisted lobectomy with lymphadenectomy yield oncologic outcomes comparable to those of open thoracotomy. However, whether selective, limited lymph node dissection is appropriate in select early-stage patients requires further prospective validation. Beyond

surgical technique itself, integrating surgery with systemic therapies to optimize long-term survival has become a central focus of international research. Key unresolved issues include the optimal neoadjuvant strategy, the role and sequencing of postoperative radiotherapy and chemotherapy in stages IIb–IIIa, and the impact of adjuvant targeted or immunotherapies on long-term survival and patterns of recurrence.

Traditional clinical research, exemplified by randomized controlled trials (RCTs), provides high internal validity through tightly controlled conditions and homogeneous patient populations. However, the strict eligibility criteria and simplified intervention protocols of RCTs often limit their generalizability to real-world clinical practice, thereby constraining their utility in guiding personalized medicine. In contrast, real-world evidence (RWE), derived from routine clinical settings, offers high external validity, greater flexibility in study design, and enhanced feasibility, making it increasingly valuable to researchers. Recent advances in health informatics and big-data analytics in oncology have led to exponential growth in the availability of high-quality RWE, enabling robust real-world studies that complement traditional trial data.

Numerous real-world studies on lung cancer have already been conducted, with large-scale analyses based on databases such as the National Cancer Database (NCDB) and the Surveillance, Epidemiology, and End Results (SEER) program gaining prominence. For instance, investigators from Weill Cornell Medicine used SEER data to assess the prognostic impact of lymph node dissection extent in patients with NSCLC tumors  $\leq 2$  cm and pathologically node-negative disease, suggesting that more extensive nodal clearance may confer oncologic benefit in those undergoing sublobar resection. Researchers at Duke University analyzed 326,228 surgically treated NSCLC patients in the NCDB (2004–2014) and questioned the appropriateness of using 30-day postoperative

mortality as the primary metric for surgical quality assessment. Additional NCDB-based studies by Osarogiagbon et al. examined prognostic factors and the value of adjuvant therapy in incompletely resected NSCLC, while Mikell et al. demonstrated a survival benefit associated with postoperative radiotherapy in patients with N2-positive NSCLC. Although real-world studies on lung cancer surgery have begun to emerge in China, they remain relatively scarce and limited by smaller sample sizes.

Real-world research on lung cancer surgery is rapidly evolving from descriptive epidemiology toward hypothesis-driven investigations, aimed at addressing pressing clinical challenges and informing integrated treatment strategies. Therefore, large-scale real-world studies in China focusing on patients with surgically resected NSCLC are warranted. Leveraging big-data technologies to analyze comprehensive, real-world clinical data will enable comparative effectiveness research across multiple therapeutic modalities, facilitate the identification of optimal treatment algorithms, refine surgical quality control systems, and support the development of preoperative risk stratification models, ultimately advancing precision oncology for NSCLC patients.

## **2 Objective**

The main objective for the NCC LungReal Phase 1 study is to establish a retrospective multicenter real-world database for patients who underwent surgery for lung cancer, and to develop an analytic framework to address clinical-relevant questions.

### **2.1 Database objective**

Phase 1 of NCC LungReal study aims to create a real-world database with the following features:

- Including at least 12 medical centers.

- Including at least 60000 patients who underwent surgical resection for lung cancer between January 2014 and December 2021.

## **2.2 Data collection objective**

Phase 1 study of NCC LungReal study aims to collect data on patient characteristics, treatment patterns, and outcomes. Efforts are taken to maximize completeness, comprehensiveness, and granularity of collected raw data.

## **2.3 Data processing objective**

Due to limited computing and human resources, priorities of data processing were determined by the Study Committee. Resources in Phase 1 study are prioritized towards 1) baseline characteristics; 2) surgery information; 3) pathology report, with the required amount of human curation and computing resources in consideration. Part of data of low priority is anticipated to be processed in Phase 2 study.

### ***2.3.1 Data with high priority***

- Structured data that could be standardized into pre-defined terminologies and values.
- Surgery record.
- Pathology report. The Study Committee determined to put processing of pathology report to high priority based on the established prognostic value of multiple pathologic features.
- Clinical Tumor-Node-Metastasis staging.
- Pathologic Tumor-Node-Metastasis staging.
- Genetic testing.
- Overall survival.

### **2.3.2 Data with low priority**

- Daily progress notes during hospital stay.
- Radiology report. The Study Committee determined to put processing of CT reports in low priority due to the very high complexity and very high inter-institutional and temporal variances of formatting and styling observed in radiology reports. Instead, the presence or absence of a certain type of radiologic examination will be extracted.

### **2.4 Data processing modules development objective**

For unstructured raw data (pathology report, etc.), multiple modules integrating pattern extraction, machine learning, and natural language processing will be developed and optimized separately to adapt to raw data with different features and complexities.

### **2.5 Analysis objective**

Qualified data were used for analyses to address the following objectives:

- The temporal trend of characteristics, treatment patterns, and outcomes for patients who received surgery for lung cancer.
- Overall survival in the whole study population, and in subgroups stratified by factors including temporal period of surgery, patient characteristics, histology, TNM stage, treatment pattern, and genetic alteration.
- Factors associated with the overall survival of patients.

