### ***3.3.2 Exclusion criteria***

Patients who meet any of the following criteria will be excluded from study entry:

- (1) Lacking raw data from the front page of the EHR.
- (2) Lacking a pathology report of the surgically resected specimen.
- (3) Lacking information required to link raw data from different sources together.

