### **3.4 Outcome measurement**

Overall survival (OS) is the primary outcome measurement.

OS is defined as the time from surgery to death from any cause. Patients who are lost to follow-up, or alive at last contact will be censored at last contact.

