#### ***4.4.1 Processing of structured raw data***

Structured data with fixed values and format, including demographics information (age, sex, blood

type, etc.), dates, laboratory test results, peri-operative prescriptions, immunohistochemistry results, and genetic testing will be standardized into given allowable values according to dictionaries and transformation rules defined by the Study Committee.

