#### ***4.4.2 Processing of pathology report***

Human and computing resources will be prioritized towards the processing of pathology reports in Phase 1 study. According to previous experience working with pathology reports, pathology report is unstructured data in the form of natural language that could be digested to logical combination of medical terminologies. Some parts of a pathology report are structured data (e.g., lymph node examination, immunohistochemistry).

Briefly, the text of a pathology report will first be sectioned by a sectioning module into “gross description”, “microscopic description of primary tumor”, “examination of lymph node”, “IHC results”, and “genetic testing results”. Text of “gross description” and “microscopic description of primary tumor” will be processed by two separate processing modules integrating pattern extraction, machine learning, and natural language processing. Text in the sections “examination of lymph node” and “IHC results” will be processed according to methods for processing structured data. Text in the section “genetic testing results” will be handed to the modules processing genetic testing results.

To achieve high precision and accuracy of processing of pathology reports, a Pathology Reference Set of structured pathology reports with a designed amount of 5000 cases will first be curated manually by certificated thoracic oncologists and data managers. This Pathology Reference Set will include all output data elements from pathology report and will serve as the gold standard to evaluate the performance of data processing.

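### OS is timed from surgery and stratified by treatment pattern with no rule for when group membership is fixed, so an ever/never grouping by postoperative therapy can gain immortal time

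*Protocol*

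**What the plan says.** - **Origin (Protocol 3.4).** "OS is defined as the time from surgery to death from any cause", and patients lost to follow-up or "alive at last contact will be censored at last contact". One origin serves all patients, with no exception.
- **Stratifiers (Protocol 2.5).** OS is to be described in the whole population and "in subgroups stratified by factors including temporal period of surgery, patient characteristics, histology, TNM stage, treatment pattern, and genetic alteration". A further objective is "Factors associated with the overall survival of patients". Treatment pattern and genetic alteration stand in one list with stage and histology. Neither is defined or given a time window.
- **Interest in postoperative therapy (Protocol 1).** Among the open questions is "the impact of adjuvant targeted or immunotherapies on long-term survival and patterns of recurrence", next to postoperative radiotherapy and chemotherapy. The Introduction closes by promising comparative effectiveness research across treatment modalities.
- **Data (Protocol 4.4.1, 4.4.2, 3.3.2).** "peri-operative prescriptions, immunohistochemistry results, and genetic testing will be standardized into given allowable values". Genetic results found in the pathology report "will be handed to the modules processing genetic testing results". "Lacking a pathology report of the surgically resected specimen" is an exclusion criterion.

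**The concern.** Stage, histology, procedure, extent of resection and neoadjuvant therapy are settled by surgery or by the resected specimen, so timing OS from surgery suits them. Postoperative therapy starts later. To be counted as treated, a patient must survive to the start. If groups are formed by whether therapy was ever given and OS runs from surgery, the wait is credited to the treated group as time without deaths, and every death during the wait goes to the untreated group. The comparison then favours treatment even if treatment does nothing.

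At stake are the survival description by treatment pattern and any association model that includes postoperative treatment. A target of at least 60,000 patients (section 2.1) does not dilute this bias; it makes a spurious difference look precise.

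**Working it through.** The protocol gives no figure for this point, so there is none to reproduce. The calculation shows how large the artefact would be under the ever/never reading when treatment has no effect.

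**Inputs**
- 5-year OS of 40%: Introduction, for outcome after surgery and adjuvant chemotherapy. Used only to set the scale.
- Assumptions, not in the protocol: exponential survival, 5 years of follow-up, delay d from surgery to start of 3 months (0.25 years), share p intended for treatment of 30% to 70%, and an alternative 5-year OS of 80%.

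**Formulas, per patient operated**
- λ = −ln(0.40)/5 = 0.1833 per year. Survival to d: S = exp(−0.1833 × 0.25) = 0.9552.
- Ever treated: deaths p(S − 0.40); person-years p[dS + (S − 0.40)/λ].
- Never treated: deaths (1 − p)(0.60) + p(1 − S); person-years (1 − p)(0.60)/λ + p[(1 − S)/λ − dS].

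**Numbers at d = 3 months, p = 50%**
- Ever treated (p cancels): 0.5552 / 3.2685 = 0.1699 deaths per person-year.
- Never treated: 0.3224 / 1.6398 = 0.1966.
- Apparent rate ratio: 0.1699 / 0.1966 = 0.86, where the truth is 1.00.
- Apparent 5-year OS: 0.40/0.9552 = 41.9% ever treated, and 0.20/(0.50 + 0.50 × 0.0448) = 38.3% never treated, where both should be 40%.

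**Range (apparent rate ratio, truth 1.00)**

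| 5-year OS | Delay | p = 30% | p = 50% | p = 70% |
|---|---|---|---|---|
| 40% | 1 month | 0.96 | 0.95 | 0.92 |
| 40% | 3 months | 0.90 | 0.86 | 0.79 |
| 80% | 3 months | 0.92 | 0.90 | 0.84 |

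A simulation of 1,000,000 patients per scenario agrees to within about 0.01. Longer delays give larger distortions, but nothing in the protocol supports such windows, so the conclusion does not use them.

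**Precision.** If 10,000 deaths accrued in two equal groups (assumption), the standard error of the log hazard ratio would be √(4/10,000) = 0.02. Even a spurious 0.95, with logarithm −0.051, would lie about 2.6 standard errors from the null.

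**Effect of the fix.** In the same simulation, time-updated exposure and a landmark at d both return rate ratios of 0.99 to 1.00 in every scenario.

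**Genetic alteration.** Among patients tested at the same delay, altered versus wild-type gives a null ratio of about 1.00 (0.997 to 1.006), because both groups had to survive to the test. What can be distorted is a comparison of tested with untested patients, and absolute OS from surgery among patients tested late.

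**The case against.** The strongest reply is that section 2.5 lists objectives and fixes no method. It names no survival curve, regression model or ever/never grouping, and handling of time-dependent exposure may sit in a statistical analysis plan that is not shown. Section 3.4 defines the outcome, not when groups are formed, and a time-dependent covariate keeps surgery as the origin. Treatment pattern could also mean only what is known at surgery: section 2.3.1 gives high priority to the surgery record but lists no adjuvant therapy, and section 4.4.1 speaks of peri-operative prescriptions. The adjuvant question is background, not an objective.

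Much of this stands. The bias is conditional, and a reader who infers that the protocol prescribes a biased comparison goes further than the text. But the protocol does fix the origin and the list of stratifiers, and it treats a factor that may arise after surgery like those settled at surgery. The Introduction's interest makes postoperative therapy a natural reading of treatment pattern, and the peri-operative wording does not exclude it.

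A reader might also infer that the genetic-alteration comparison carries the same bias. The documents do not support that. The stratifier is alteration, not tested versus untested. Results come at least partly from the pathology report, and a report of the resected specimen is required for entry, which points to testing at or soon after surgery. Testing prompted by relapse, which no section mentions, would select patients with a worse prognosis and could push the other way.

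**Conclusion.** The point holds in a conditional form, limited to postoperative treatment. If treatment pattern includes it and groups are formed as ever/never from surgery, the treated group gains immortal time. With no true effect, 5-year OS of 40% and a 3-month delay, the apparent rate ratio is about 0.79 to 0.90 across treated shares of 30% to 70%; with 5-year OS of 80% it is 0.84 to 0.92. Delay, share, exponential survival and the 80% are assumptions, and the 40% is not this cohort's figure. Factors known by surgery carry no such bias. For genetic alteration, the protocol needs only a rule on late results and untested patients. The change should be made, because a few sentences remove the ambiguity.

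**What to change.** In sections 2.5 and 3.4, or there by explicit reference to the statistical analysis plan:

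1. Define treatment pattern, and the time window in which a treatment or genetic result counts.
2. State that groups are timed from surgery only for factors settled by surgery or by the resected specimen: procedure, extent of resection, neoadjuvant therapy, stage and histology.
3. For postoperative treatment, set a fixed landmark in advance: classify by status at the landmark, count OS from it and report the deaths before it. Alternatively, enter treatment as a time-dependent covariate.
4. For genetic alteration, compare altered with wild-type among tested patients, use delayed entry at the test date for results obtained well after surgery, and do not use untested patients as a comparator.

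**Cost.** The text change is small. With a landmark, early deaths drop out of these comparisons (1 − 0.9552 = 4.5% of patients at 3 months under the 40% assumption), and patients who start after the landmark count as untreated. Treatment start dates and genetic test dates must be available; section 4.4.1 mentions dates only in general, so this should be confirmed first. Neither method removes confounding by the reasons for giving treatment.

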## **3 Study design**

### **3.1 Description of the study**

Phase 1 study of NCC LungReal study is a retrospective, multicenter, electronic health record

(EHR)-based, real-world study. Figure 1 illustrates the study design.

Phase 1 study of NCC LungReal study enrolls patients who underwent surgical resection for lung cancer during the time period from January 2014 to December 2021.

## **3.2 Medical centers enrollment**

### ***3.2.1 Inclusion criteria***

No limitation on type, level, location, or volume is set for enrollment of participating medical centers.

All medical centers whose raw data are submitted to the National Cancer Information Database (NCID) that meet the predefined quality standards will be screened for study entry.

### ***3.2.2 Exclusion criteria***

Medical centers whose raw data submitted to NCID are incomplete, erroneous, or of low quality, as defined by meeting any of the following criteria, will be excluded:

- (1) Proportion of cases that lacks front page of EHR, or cases whose front page is filled with unrelated text or garbled codes >40.0%.
- (2) Proportion of cases that lack a pathology report of 60 or more Chinese characters, or cases whose pathology report is filled with unrelated text or garbled codes >40.0%.
- (3) Proportion of cases that lack internal linkages of raw data from different sources >40.0%.

## **3.3 Patient enrollment**

### ***3.3.1 Inclusion criteria***

Patients who were admitted to the enrolled participating medical centers between January 2014 to December 2021 and met any of the following criteria are eligible for study entry:

- (1) Diagnosis of lung cancer and presence of lung surgery record.

- (2) Diagnosis of lung cancer and presence of pathology report containing  $\geq 60$  Chinese characters.
- (3) Diagnosis of lung cancer and presence of lung surgery in the data field of “operation” in the front page of EHR.
- (4) Diagnosis of lung cancer and admitting department is (thoracic) surgery department.

“Diagnosis of lung cancer” requires any one of the following:

- Diagnoses on the front page of EHR include typical Chinese terminology for “lung cancer” and/or “lung malignancy” defined by the Study Committee.
- ICD-9 code on the front page of the medical record includes “162.”
- ICD-10 code on the front page of the medical record includes “c34.” or “c39.9”.
- ICD-O-3 code on the front page of the medical record includes any of xxxx/3 code in the list of 2015 WHO classification of lung tumors.
- Name of the surgery included typical Chinese terminology for lung cancer surgery, determined by the Study Committee.
- Pathology diagnosis includes terminologies for “lung cancer” and/or “lung malignancy” defined by the Study Committee.

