#### ***4.3.1 Accuracy of patient enrollment***

The accuracy of patient enrollment is defined as the proportion of patients enrolled that were confirmed by a human check.

As the lack of sex, age, and poor quality of internal linkage can be easily checked automatically, human resources are prioritized towards checking the presence of pathology reports for surgical specimens and the diagnosis of lung cancer. Trained data managers will check the raw text of the pathology report of enrolled patients to determine the presence of pathology reports for surgical specimens and the diagnosis of lung cancer. A total of 12,000 cases will be stratified-sampled from the included medical centers for accurate enrollment.

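### The cohort is defined by date of resection in 2.1 and 3.1 but selected by date of admission in 3.3.1, so patients operated on earlier or elsewhere can enter with left-truncated overall survival

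*Protocol*

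**What the plan says.** Two sections of the protocol date the operation. The database objective (2.1) reads "Including at least 60000 patients who underwent surgical resection for lung cancer between January 2014 and December 2021", and the study description (3.1) says that the study "enrolls patients who underwent surgical resection for lung cancer during the time period from January 2014 to December 2021".

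The criteria that select patients (3.3.1) date something else: "Patients who were admitted to the enrolled participating medical centers between January 2014 to December 2021 and met any of the following criteria". Any one of four routes is then enough. Two of them need no record of surgery:

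- Route 2: "Diagnosis of lung cancer and presence of pathology report containing" at least 60 Chinese characters.
- Route 4: "Diagnosis of lung cancer and admitting department is (thoracic) surgery department".

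The exclusion in 3.3.2 that bears on this is "Lacking a pathology report of the surgically resected specimen". It gives no date for the report and does not say which hospital must have issued it.

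For the primary outcome, 3.4 states "OS is defined as the time from surgery to death from any cause". It adds a censoring rule but no rule for when a patient comes under observation. For the manual check of enrolment, 4.3.1 says that "human resources are prioritized towards checking the presence of pathology reports for surgical specimens and the diagnosis of lung cancer".

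**The concern.** An admission in the window is not the same event as a resection in the window. Section 4.6 says that visits and re-admissions to participating centres are exported from the source database, so later admissions of operated patients are in the data. A patient who qualifies only through a later admission had to survive from surgery to that admission. If OS is counted from surgery, that stretch contains no possible death, yet it is treated as time at risk. This is left truncation, often called immortal time.

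OS is the primary outcome. Two of the three analysis aims in 2.5 concern OS, one of them by period of surgery, and the third includes time trends in outcomes. Patients selected in this way would also count toward the 60,000 target, although 2.1 reserves that count for resections in the window.

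**Working it through.** The protocol gives no figure to reproduce on this point; 60,000 is a target count without a formula. The check has two parts.

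**1. Reading the rules together.** Take a patient resected at an enrolled centre before 2014, with the specimen report on file, who is re-admitted in 2015 with lung cancer on the front page.

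| Rule | Outcome for this patient |
|---|---|
| 2.1 and 3.1 (resection in the window) | outside the cohort |
| 3.3.1 (admission in the window, any one route) | eligible, for example by route 2 |
| 3.3.2 (front page, specimen report, linkage) | not excluded |
| 3.4 (OS from surgery) | counted from before 2014 |
| 4.3.1 (specimen report, diagnosis) | passes both items named |

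Now take a patient resected inside the window at a non-participating hospital and admitted later to an enrolled centre, with a consultation report on the specimen. Here 2.1 and 3.1 do not help either, because they do not name the operating centre. The coverage check in 4.3.2 compares against patients who meet the enrolment criteria, so it carries the same ambiguity.

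**2. Illustrative size.** Inputs:

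- True 5-year OS, S: about 40% is the background figure in section 1; 60% and 80% are assumed.
- Share f of patients operated on before their qualifying admission: not in the documents; assumed 1%, 5% and 10%.
- Delay from surgery to entry: not in the documents; assumed uniform on 0 to 5 years.
- Hazard after entry: either the ordinary rate λ = −ln(S)/5, or an assumed relapse rate of 0.35 per year.
- Constant hazards and no censoring.

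A late entrant with delay d and hazard h after entry is alive at 5 years with probability exp(−h(5 − d)). Averaged over d, this is P = (1 − exp(−5h))/(5h). The apparent 5-year OS is (1 − f)·S + f·P.

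- Ordinary hazard, S = 60%: 5λ = 0.511, P = 0.400/0.511 = 0.783.
- Ordinary hazard, S = 80%: 5λ = 0.223, P = 0.200/0.223 = 0.896.
- Ordinary hazard, S = 40%: 5λ = 0.916, P = 0.600/0.916 = 0.655.
- Relapse hazard: 5h = 1.75, P = (1 − 0.174)/1.75 = 0.472.

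| True S | Hazard after entry | f = 1% | f = 5% | f = 10% |
|---|---|---|---|---|
| 60% | ordinary | 60.2% | 60.9% | 61.8% |
| 60% | relapse 0.35 | 59.9% | 59.4% | 58.7% |
| 80% | ordinary | 80.1% | 80.5% | 81.0% |
| 80% | relapse 0.35 | 79.7% | 78.4% | 76.7% |
| 40% | ordinary | 40.3% | 41.3% | 42.5% |
| 40% | relapse 0.35 | 40.1% | 40.4% | 40.7% |

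Example: S = 60%, f = 10%, ordinary hazard: 0.9 × 0.600 + 0.1 × 0.783 = 0.618. The sign depends on whether P lies above or below S. The same relapse hazard pulls a true 60% or 80% down but a true 40% slightly up. At f = 1% the largest departure is 0.01 × (0.800 − 0.472) = 0.3 points.

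**Does delayed entry repair it?** With S = 40%, f = 10%, a fixed delay of 2 years and ordinary hazard, S(2) = exp(−0.183 × 2) = 0.693. A late entrant's 5-year survival is then 0.40/0.693 = 0.577, and the apparent OS is 0.9 × 0.400 + 0.1 × 0.577 = 41.8%. A simulation of 400,000 patients also gave 41.8%. Counting risk time only from entry returned 40.0%.

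**The case against.** The strongest reply is that the protocol must be read as a whole. Section 3.1 sits inside the study design and limits the study to resections in the window, so pre-2014 surgery is already barred. Routes 1, 3 and 4 refer to a surgery record, the front-page operation field and a surgical admitting department, which suggests that a surgical stay was meant. The requirement for a resected-specimen report probably removes many patients operated on elsewhere, because 4.1 takes raw data from the participating centres' own systems. On this view only a drafting gap remains.

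Much of this stands, and it rules out several stronger readings:

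- A reader might infer that the study deliberately enrols prevalent patients and that its OS is therefore biased by immortal time. The documents do not support this: 2.1 and 3.1 show the opposite intent, and the number affected is unknown.
- A reader might infer that the bias must be upward. That holds only if late entrants have ordinary hazard after entry.
- A reader might infer that the manual check of 12,000 cases cannot detect such patients. The text says less: surgery date and place are not named. Nothing forbids looking at them, and dates are standardized as structured data under 4.4.1.
- Stays that span either end of the window are misclassified at the edge. That is a minor matter and not immortal time.

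The reply does not remove the conflict. Nothing in 3.3.1 says that the admission is the one at which the resection was done. Even with 3.1 read as binding, a patient operated on elsewhere in 2014–2021 and admitted later is not stopped. A statistical analysis plan might add delayed-entry handling, but it cannot settle which of two protocol definitions of the cohort applies.

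**Conclusion.** The protocol contradicts itself on who is in the cohort: resection date in 2.1 and 3.1, admission date in 3.3.1. The exclusions do not close the gap, and the primary outcome runs from the event that the selection rule leaves undated. This should be corrected in the protocol.

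What follows for OS is a possible bias of unknown size and sign. Under the assumed shares of 5% to 10%, the departure at a true 60% is about +0.9 to +1.8 points with ordinary hazard, or −0.6 to −1.3 points with the assumed relapse hazard. At a 1% share it is at most about 0.3 points across the cases shown. These figures rest on assumed shares, delays and hazards, without censoring. The conclusion rests on the conflict in the text and not on them.

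**What to change.** Make 3.3.1 match 3.1. Require that the lung cancer resection from which OS is counted was performed at an enrolled centre, during the qualifying admission, with a surgery date from January 2014 to December 2021. The surgery date then sets the window in place of the admission date. Apply this as an automatic filter on surgery date and operating centre, and add both items to the check in 4.3.1. There is no need to restrict to a patient's first resection; the protocol contains no such limit, and adding one would change how second primaries are handled.

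Alternatively, keep patients who entered through a later admission, record their entry date, and use delayed-entry risk sets for OS. This corrects the bias only if time of entry is unrelated to later hazard, which fails for patients re-admitted because of relapse. The filter is therefore the safer choice.

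The cost is one sentence and one filter. Surgery records are already high priority under 2.3.1, and dates are structured data under 4.4.1. The downside is that a few re-admitted patients leave the database and the 60,000 count.
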